#### Implementation outcomes

We will also monitor the implementation process’s uptake, feasibility, acceptability, and fidelity of the CombinADO strategy. This will measure uptake and utilization of intervention components by AYAHIV among AYAHIV in care at intervention and control sites and implementation fidelity by HCWs and KIs. Both acceptability and feasibility will be assessed qualitatively in interviews; fidelity will be assessed through monthly observational assessments and review of health facility registers conducted by study staff. Additional questionnaires related to cost/cost-effectiveness will also be conducted with a subset of HCWs at each site.

### Data collection

Trial outcomes comprise of data collected from (1) a questionnaire developed during the formative phase administered to AYAHIV in a private space by trained fieldworkers at the post-intervention assessment, (2) exit interviews with AYAHIV attending care at adolescent-focused services during intervention implementation, (3) semi-structured interviews with AYAHIV caregivers attending caregiver support groups, (4) semi-structured interviews with HCWs and KIs, (5) costing questionnaire with a subset of HCWs, (6) retrospective abstraction of AYAHIV medical records in the 12 participating facilities for data on HIV care and treatment, (7) collection of aggregate facility-level routinely collected data for retention, (8) observational data collected by study staff on time taken for clinic activities, (9) collection of process indicators on implementation intervention, and (10) blood sampling in AYAHIV at the post-intervention assessment for real-time viral load testing and dried blood spot (DBS) for future TDF-DP drug level testing.

All procedures for data collection (regardless of source) will be outlined in standard operating procedures (e.g., for DBS, specimen transport or questionnaire administration), from which all study staff will be trained ahead of study implementation at each site. With oversight from the Mozambique-based Study Coordinator, the CombinADO Field Manager will work with a dedicated team to ensure consistent administration (fidelity of delivery) of the study intervention across the 12 study sites during the 12 months of implementation.

The study team, including all staff collecting data from participants as well as participating HCWs, will be trained in an emergency protocol to be able to identify participants requiring additional support and follow-up (medical, social, psychological) as well as the process for referrals for existing support services that are in place at each health facility. A further description of measurements that will be collected through the different processes is outlined in Table 5.

**Table 5 Tab5:** Study data collection sources, information collected, and timing of collection for all CombinADO study participants

Measurement	Information collected	Participants	Time
Survey questionnaire	o Basic demographic information, education, and vocation information o HIV, STI, ART, reproductive health beliefs and literacy o Adherence and adherence self-efficacy o Youth readiness for independent health care o Relationship/marital status o Mental health o Life events o Substance use o Sexual risk o Reproductive health, including pregnancy and parenthood o Interpersonal violence o Partner, family, and social support o HIV stigma/disclosure o Experience with COVID-19 o Uptake of CombinADO strategy intervention components o Feasibility, acceptability, and appropriateness of all strategy intervention components	AYAHIV	T3
Exit interviews	o Experiences and satisfaction with the services received and various intervention components	AYAHIV	T2
Semi-structured interviews	o Perceived benefits and challenges of attending the support groups o Comfort taking part in the support group o Satisfaction with current support groups structure o Recommendations for refining the existing support groups	Caregivers	T2
	o Experience implementing the intervention, including time spent providing care to AYAHIV o Impact of the intervention on facility and delivery of health services o Met and unmet needs of the AYAHIV population seeking services o Adoption, implementation, maintenance, reach, feasibility, acceptability appropriateness, and fidelity of the intervention various components	HCWs and KIs	T1–T3
Costing questionnaire	o The daily schedule at the health facility o Time spent working across various clinic activities, including consultations with AYAHIV	HCWs	T1 and T2
Blood sampling	o Blood for real-time viral testing o Dried blood spot (DBS) samples for TDF-DP drug-level testing	AYAHIV	T3
Abstraction of AYAHIV routine data	o Date of HIV diagnosis o ART start date o Current ART regimen o Intercurrent hospitalizations o Most recent HIV RNA viral load and CD4 results o Pharmacy dispensing and refill information o Most recent visit date o Retention in care	Clinic records	T3
Monitoring of implementation process	o Number and duration of support groups conducted o Number of AYAHIV and caregivers attending support groups (new/returning) o Curriculum materials and intervention content delivered o Number of AYAHIV expected within the clinic and number interacting with various components of the intervention package o Number of clinic-based peers trained/retained o Number of support group facilitators trained/retained o Number of HCWs trained on new service components o Number of radio and print materials posted/broadcast in the community	Site staff	T2

Time: *T1* pre-intervention, *T2* intervention implementation, *T3* post-intervention implementation

### Data management

During the study, study staff will have access to research records. In addition, members of the Mozambique Ethics and Scientific Review Committee (CNBS), the Columbia University Irving Medical Center (CUIMC) IRB, study monitors and other additional local and US regulatory agencies like the Office for Human Research Protections (OHRP) as well as the study sponsor, National Institutes of Health (NIH), may look at the research records.

All digital data collection tools will be encrypted, password protected, and collected from the staff at the end of each day to be stored in locked filing cabinets at the study sites. All datasets will be stored on SurveyCTO during data collection and accessed on password-protected computers certified by Columbia University IT. All hard copies of all source documents, data collection tools, and study logs be kept in a secure locked cabinet in a locked office at the study site. No participant identifying information will be documented on any of these data sources; participants will only be identified by a unique participant ID (PID). All documents with personal identifying information will be stored separately from all study data and accessible to specific research staff (data collection staff, study coordinator, and study monitors). All DBS samples collected at the post-intervention assessments will be stored for the duration of this study at the INS lab based in Nampula until required for TDF-DP drug level testing planned for end of the study . No blood samples will be stored or shared for future use outside of this protocol.

At the end of the study, all records will continue to be kept in a secure location for as long a period as dictated by the reviewing IRB, Institutional policies, or sponsor requirements.

### Data analysis

#### Populations for analyses

The primary outcome (and secondary adherence outcome) will use an intention to treat population of all participants consenting to the post-intervention assessment who complete a questionnaire and VL test. The per-protocol population for the primary outcome (and secondary adherence outcome) will define exposure to the intervention based on AYAHIV-stated engagement in one or more component of the CombinADO intervention during interviews at the post-intervention assessment. The secondary retention in care endpoint will use the eligible (based on inclusion criteria) population of all AYAHIV registered at the clinic site during a 15-month period extending from 6 months before the start of the intervention period to the end of the intervention period. Data for the secondary retention in care endpoint will use routine data abstracted from clinic records. This definition will exclude AYAHIV, who newly initiated ART at the site in the final 6 months before the end of the intervention period.

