#### AYAHIV

Up to 2400 AYAHIV (maximum of 200 AYAHIV per site) will be recruited to take part in a one-time post-intervention assessment at 12 months post-intervention implementation and up to 720 AYAHIV (maximum of 60 per site) in exit interviews during intervention implementation. Clinic staff will work with on-site study staff to review the daily schedule and list potentially eligible AYAHIV who have appointments. During the clinic visits at the 12 sites, clinic staff will consecutively approach and directly present the study to those 18 years and older or the adult caregiver for adolescents younger than 18. Both interested AYAHIV and caregivers will be referred to the study staff for recruitment. The study staff will give AYAHIV more details on the study procedures, screen AYAHIV for eligibility using criteria in Table 1, and finally obtain informed consent from AYAHIV 18 years and older or assent from adolescents aged 12–17 of consenting caregivers. Eligible adolescents aged 10–11 will be given information sheets that describe the study, and consent for their participation will be obtained from their caregivers. The study staff will note reasons for ineligibility and/or refusal and AYAHIV will be replaced until target sample is reached at each site.

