**Secondary**			
To evaluate the efficacy of the CombinADO strategy on the rate of retention in care among AYAHIV receiving HIV care at 12 health facilities in Nampula Mozambique	Retention in care defined as objective evidence of engagement in the preceding 90 days among AYAHIV in care at intervention and control sites	Increases in retention in care is a causal intermediate (mediator) through which the CombinADO strategy may increase HIV viral suppression	Different elements of the CombinADO strategy are likely to support AYAHIV’s retention in care during the intervention period
To evaluate the efficacy of the CombinADO strategy on the rate of adherence to ART among AYAHIV receiving HIV care at 12 health facilities in Nampula Mozambique	Self-reported using the Wilson measure; TDF levels on a subset of participants in care, selected retrospectively in a case-control substudy comparing AYAHIV who have VL < 50 copies/mL, versus those with VL ≥ 50 copies/mL	Increases in ART adherence is a causal intermediate (mediator) through which the CombinADO strategy may increase HIV viral suppression	Different elements of the CombinADO strategy are likely to support AYAHIV’s adherence to ART during the intervention period
To assess the uptake, feasibility, and acceptability of the CombinADO strategy at 12 health facilities in Nampula Mozambique	Uptake and utilization of intervention components by AYAHIV among AYAHIV in care at intervention and control sites; implementation fidelity by health care workers and key informants	Uptake and implementation of the intervention is an intermediate (mediator) through which the CombinADO strategy may increase HIV viral suppression	Inadequate uptake and implementation of the intervention and/or components can limit efficacy of the intervention
To estimate the cost and incremental cost-effectiveness of the CombinADO strategy at 12 health facilities in Nampula Mozambique	Incremental cost per additional case of viral suppression < 50 copies/mL at 12 months	HIV viral suppression provides an objective summary measure of intervention effectiveness	The CombinADO strategy is hypothesized to increase viral suppression through increases in retention in care and/or adherence to ART in the target population

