#### Statistical analysis

Descriptive statistics will be presented with frequency (percent) or median (interquartile range) depending on the type and will provide overall and by allocation arm. Review of data distributions will be undertaken prior to applying any inferential statistics requiring specific assumptions and methods revised or corrective procedures undertaken. Covariates and specific details of analysis will be fully specified before database closure in a detailed SAP developed by the study statistician and study team. All statistical tests will be two-sided with nominal *α* = 0.05. Study endpoints are binary and will be approached in a similar way. The primary outcome analysis will compare AYAHIV virologic suppression at 12 months post-intervention implementation in intervention versus control sites using generalized estimating equations under a binomial model, with a log link and robust standard errors, providing unbiased marginal estimates of the intervention effect while adjusting for within-cluster correlations. Clustering will be by site using an exchangeable correlation structure. Estimates will be reported as risk ratios (RR) with robust 95% confidence intervals and *p*-values assessed at *α* = 0.05 for all comparisons. No additional adjustment variables will be included in the primary analysis. In subsidiary analyses, we will include covariate adjustment based on confounders selected a priori using direct acyclic graphs. Sensitivity analysis will address potential heterogeneity in clustering by evaluating endpoint models under different assumed correlation structures. Missing outcome data will be handled by complete case analysis in the first case and then by sensitivity analysis substituting alternate outcome values for missing data. Missing data in covariates will be handled by multiple imputations using chained equations. Analysis of secondary endpoints is not conditional on the outcome of the primary endpoint. Secondary endpoints will be approached identically as the primary endpoint. Planned subgroup analyses, which include by age group [10–14, 15–19, 20–24], sex, pregnancy status during the intervention period among females, duration of prior ART use, and ART regimen, will be carried out for primary and secondary outcomes using the same approach as the previously described. Exploratory analyses will include:

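### The primary set labelled intention to treat holds only youth who attend, consent and have a VL test at month 12, so randomization does not protect the contrast and the missing-outcome analysis has essentially nothing to act on

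*Protocol article*

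**What the plan says.** All references are to the Protocol article.

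- **Analysis set.** Populations for analyses defines, for the primary and adherence outcomes, an "intention to treat population of all participants consenting to the post-intervention assessment who complete a questionnaire and VL test". Retention alone is analysed on all eligible registered AYAHIV.
- **Recruitment.** Under Participants and recruitment (AYAHIV), there is a "one-time post-intervention assessment at 12 months post-intervention implementation". The sampling route is: "Clinic staff will work with on-site study staff to review the daily schedule and list potentially eligible AYAHIV who have appointments". For those ineligible or refusing, reasons are noted and "AYAHIV will be replaced until target sample is reached at each site". Table 2 shows no pre-intervention assessment of AYAHIV.
- **Mechanism.** Table 4 says of the retention endpoint: "Increases in retention in care is a causal intermediate (mediator) through which the CombinADO strategy may increase HIV viral suppression". For the primary endpoint it names retention, adherence or both as the route, and it words that endpoint as suppression among AYAHIV in care.
- **Missing data.** Statistical analysis says: "Missing outcome data will be handled by complete case analysis in the first case and then by sensitivity analysis substituting alternate outcome values" for the missing data. The same section describes the GEE estimate of the intervention effect as unbiased.

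**The concern.** Randomizing clinics balances the populations the clinics serve at allocation. It does not balance groups that form later through attendance, consent and testing. Here all three decide who enters the primary analysis, and attendance is something the strategy is meant to change. Youth whom the strategy keeps in care can be sampled at intervention clinics, while their counterparts at control clinics, who dropped out, are largely absent. The two samples may then differ in make-up for reasons unrelated to suppression among comparable patients. An exchangeable correlation structure and robust standard errors deal with clustering and leave this selection untouched.

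The stated safeguard does not help. The set admits only people with a completed VL test, so a rule for substituting missing VL outcomes finds almost none. Losses before testing (not attending, refusing, enrolled but not tested) lie outside the set.

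At stake is the reading of the headline result. A contrast among attenders can understate or overstate what the strategy does for the clinics' AYAHIV. If the cost per additional suppressed case uses the same sample, it carries the same distortion.

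**Working it through.** The plan gives no figure for this selection, so there is none to reproduce. The check has two parts.

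**1. Passages side by side.** Entry condition: completed questionnaire and VL test. Missing-data rule: complete cases first, then substituted values. Within the set, the number missing the primary outcome is 0 by definition, so the two analyses coincide. Small exceptions remain, such as an invalid result after a completed test or item non-response on the adherence scale.

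**2. Size of the selection effect (illustration).**

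Inputs from the document:
- Control retention r0 = 55%, the middle of the assumed 50–60% (Sample size and power, Retention). With 220 per clinic, 110 to 132 meet the 90-day definition and 88 to 110 do not.
- Control suppression 65% and design effect 16 points, giving 81% (Sample size and power, Primary outcome).

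Assumptions not in the document:
- Everyone who attends under control would also attend under the intervention.
- The intervention retains a further dr = 5 to 15 points, who suppress at s = 40 to 60%.
- Sampling reflects retention.
- On the register scale, those not retained count as unsuppressed.

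Formulas, with direct effect d in those who attend under either arm:
- Attender contrast = [r0(0.65 + d) + dr·s]/(r0 + dr) − 0.65
- Break-even d (contrast zero) = dr(0.65 − s)/r0
- Register contrast = r0·d + dr·s

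Central case with d = 0.16: (0.55×0.81 + 0.10×0.50)/0.65 = 0.4955/0.65 = 76.2%, or +11.2 points. With d = 0: (0.3575 + 0.05)/0.65 = 62.7%, or −2.3 points.

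| dr | s | Attenders, d = 16 | Attenders, d = 0 | Break-even d | Register, d = 0 |
|---|---|---|---|---|---|
| 5 | 60% | +14.3 | −0.4 | 0.5 | +3.0 |
| 10 | 50% | +11.2 | −2.3 | 2.7 | +5.0 |
| 15 | 40% | +7.2 | −5.4 | 6.8 | +6.0 |

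The first and last rows are the extremes of the attender contrast over this grid. The register contrast with d = 0 runs from +2.0 (0.05×0.40) to +9.0 (0.15×0.60). Moving control retention to 50% or 60% changes the central d = 16 result only to +10.8 (0.455/0.60 = 75.8%) or +11.6 (0.536/0.70 = 76.6%).

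The bias can also run the other way. If the extra 10 points retained suppress at 90% (assumed), the contrast is (0.4455 + 0.09)/0.65 = 82.4%, or +17.4 points.

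**The case against.** The strongest reply is that the in-care question is declared. The abstract, the primary objective and Table 4 all confine suppression to AYAHIV attending or receiving care, and retention has its own endpoint on the registered population. The intention-to-treat label can be read, against the per-protocol set defined beside it, as analysis by clinic allocation regardless of uptake. This stands as a defence of asking the question. It does not defend the label or the claim of no bias, and reporting retention separately does not combine with suppression into one randomized comparison.

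The missing-data rule also covers the secondary endpoints, and retention uses another population, so the rule is empty only for the primary outcome. Detail is deferred to a SAP that is not at hand, but the conflict between the set and the rule lies in the article itself.

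Three stronger readings are tempting and not supported:
- **That the primary contrast will have the wrong sign.** This needs almost no direct effect. Table 4 names adherence as a mechanism too, and at the design effect the illustration gives attenuation.
- **That anyone lost from care cannot enter.** Patients who lapsed and returned, and those who registered during the trial, may hold appointments. The 50–60% is a 90-day engagement figure and not a probability of being sampled.
- **That the biweekly support groups make intervention patients more likely to be sampled.** Nothing says that group meetings are appointments or feed the daily schedule.

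**Conclusion.** The point holds. The set is conditioned on attendance, consent and testing after allocation, and attendance is a stated target of the strategy. The contrast is therefore not protected by randomization, and describing it as intention to treat and unbiased is wrong.

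The direction cannot be settled from the documents. If the extra youth retained suppress less well than the others, a true 16-point effect appears as about +7 to +14 points under the stated assumptions. The sign turns only if the direct effect is below about 2.7 points in the central case (0.5 to 6.8 over the grid). If they suppress better, the contrast is inflated. The retention gain and the suppression of those retained are assumptions; only the control retention, control rate and design effect come from the article.

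The missing-outcome sensitivity analysis is essentially empty for the primary outcome. That follows from the text and needs no assumption.

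**What to change.** (a) Rename the set, for example the month-12 assessed in-care population, and remove the intention-to-treat and unbiased wording. The primary analysis itself can stay. Cost: wording only.

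(b) Define the sensitivity-analysis set as all eligible AYAHIV enrolled at month 12 and, where logged, approached, whether or not a VL was obtained, and apply the substitution there. Reasons for refusal and ineligibility are already to be noted. Cost: a log by site that can be counted.

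(c) Where individual-level routine records are abstracted, add a supportive analysis on the registered population already defined for retention. Score success as engagement within the last 90 days and a most recent VL below 50 copies/mL. Table 5 lists retention and "Most recent HIV RNA viral load and CD4 results" among the abstracted items. Report VL coverage by arm and vary the treatment of those with no VL. First reconcile that population's window: it is given as 15 months, yet 6 months before the start plus a 12-month intervention makes 18.

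Cost of (c): one further analysis if the records are individual-level. Data collection lists medical-record abstraction but also describes the retention data as aggregate at facility level, so feasibility must be confirmed. Routine VL coverage and dates vary by site and may differ by arm, and the registered population also admits people who registered after the start. It should therefore be supportive only.

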#### Effectiveness outcomes

The primary outcome is viral suppression < 50 copies/mL at 12 months post-intervention implementation among AYAHIV at intervention and control sites, which will be assessed through real-time viral load testing.

Secondary outcomes include:

(1) ART adherence will be measured by using a validated Wilson self-report ART adherence measure administered on all AYAHIV participating in the one-time post-implementation assessment at 12 months post-intervention implementation [26, 27]. In addition, TDF levels will be measured on a subset of participants in care selected retrospectively in a case-control sub-study comparing AYAHIV who have VL < 50 copies/mL, versus those with VL ≥ 50 copies/mL. The Wilson measure has previously been implemented in this setting to assess ART adherence among AYAHIV during the first phase of the CombinADO study [12]. (2) Retention in care will be measured as objective evidence of engagement in the preceding 90 days among AYAHIV in care at intervention and control sites abstracted from routine clinic records.

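### The primary set requires a completed questionnaire as well as a viral load, so as written it can exclude participants whose primary outcome is known

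*Protocol article*

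**What the plan says.** Under Populations for analyses, the Protocol article states that "The primary outcome (and secondary adherence outcome) will use an intention to treat population", made up of "all participants consenting to the post-intervention assessment who complete a questionnaire and VL test". This is one set for two outcomes, with both measurements as entry conditions.

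The two outcomes have different sources. Effectiveness outcomes describes viral suppression as an endpoint "which will be assessed through real-time viral load testing". Self-reported adherence comes from a "validated Wilson self-report ART adherence measure administered on all AYAHIV participating in the one-time post-implementation assessment". Table 5 lists blood sampling and the survey questionnaire as separate measurements.

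For the primary model, Statistical analysis says: "No additional adjustment variables will be included in the primary analysis". On missing data it says: "Missing outcome data will be handled by complete case analysis in the first case and then by sensitivity analysis substituting alternate outcome values". Missing covariates are to be multiply imputed.

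The interview has one further use. The per-protocol population is defined from "AYAHIV-stated engagement in one or more component of the CombinADO intervention during interviews at the post-intervention assessment".

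**The concern.** The questionnaire supplies nothing that the primary estimate needs, yet it is a condition for entering the primary analysis. A participant who consents, attends and gives a usable blood sample has an observed primary outcome. Under the stated rule, that outcome is not used if the questionnaire is not completed. The same rule works in reverse for self-reported adherence, where an answered measure is set aside for want of a viral load.

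The main issue is selection. Participants and fieldwork staff know the allocation (Randomization and blinding). The questionnaire has 16 listed topics, among them substance use, sexual risk, violence, stigma and "Uptake of CombinADO strategy intervention components". Completing it could be related to engagement in care, and so to suppression, and the relation could differ by arm. Making completion an entry condition adds a post-randomisation selection step to an analysis labelled intention to treat, with nothing gained for the primary outcome.

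The rule also fits badly with the missing-data plan. If everyone in the set has a viral load, a substitution analysis for missing viral loads has little or nothing to work on.

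**Working it through.** **Step 1: the passages side by side (Protocol article).**

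| Element | Needs viral load | Needs questionnaire | Where |
|---|---|---|---|
| Primary outcome | yes | no | Effectiveness outcomes |
| Primary model covariates | none | none | Statistical analysis |
| Self-reported adherence | no | yes | Effectiveness outcomes |
| Per-protocol version of the primary analysis | yes | yes (stated engagement) | Populations for analyses |
| Stated set for primary and adherence outcomes | yes | yes | Populations for analyses |

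No other rule brings back a participant with a viral load and no questionnaire. The missing-outcome rule does not apply, because the outcome is observed. The imputation rule concerns covariates, and the primary model has none. The replacement rule under Participants and recruitment covers only ineligible people and those who refuse.

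**Step 2: effect on power.** Inputs from Sample size and power: 12 clinics (6 per arm), m = 100 per clinic, 65% v 81%, ICC 0.05, two-sided α = 0.05.

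- Effective n per arm = 6m / (1 + (m − 1) × ICC) = 600 / 5.95 = 100.84.
- Power = Φ{[0.16√n − 1.96√(2 × 0.73 × 0.27)] / √(0.65 × 0.35 + 0.81 × 0.19)} = Φ{(1.607 − 1.231) / 0.618} = 72.9%.

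The plan states more than 80%. This calculation does not reproduce that figure at ICC 0.05, but gives 80.4% at ICC 0.04, the low end of the stated range. That is a separate matter; only the change in power is used here. The share f of participants with a viral load but no questionnaire is assumed, since the article gives none.

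| f | Power, ICC 0.05 | Power, ICC 0.04 |
|---|---|---|
| 0% | 72.9% | 80.4% |
| 2% | 72.7% | 80.3% |
| 5% | 72.5% | 80.0% |
| 10% | 72.1% | 79.6% |
| 20% | 71.2% | 78.5% |

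Between-clinic variation dominates, so even a 20% loss costs less than 2 points.

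**Step 3: possible bias.** For each arm, let p be suppression among all with a viral load, f the share without a questionnaire and s suppression in that share. The analysed proportion is q = (p − f·s) / (1 − f). If s = p, nothing moves. All values of f and s below are assumptions.

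| Scenario | All with a viral load: difference, RR | Analysed: difference, RR |
|---|---|---|
| A. s = 50% in both arms, f = 5% in both | 16.0 points, 1.246 | 16.8 points, 1.256 |
| B. s = 50% in both arms, f = 5% intervention, 2% control | 16.0 points, 1.246 | 17.3 points, 1.265 |
| C. s = 50% in both arms, f = 10% intervention, 5% control | 16.0 points, 1.246 | 18.7 points, 1.284 |
| D. Dropped 20 points below completers, f = 3% intervention, 8% control | 17.0 points, 1.268 | 16.0 points, 1.246 |
| E. Dropped 20 points below completers, f = 5% in both | 16.0 points, 1.250 | 16.0 points, 1.246 |

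Example, B: intervention (0.81 − 0.05 × 0.50) / 0.95 = 0.8263; control (0.65 − 0.02 × 0.50) / 0.98 = 0.6531; RR = 1.265.

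In D and E the completers are set at 81% and 65%. For D, the full-group values are 0.97 × 0.81 + 0.03 × 0.61 = 0.804 and 0.92 × 0.65 + 0.08 × 0.45 = 0.634. For E they are 0.80 and 0.64.

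A to C move the contrast away from the null and D towards it. E leaves the difference unchanged and barely moves the RR.

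**The case against.** The strongest reply is that the sentence was never meant as a hard joint filter. It covers two outcomes at once and may simply describe people who went through the single post-intervention assessment, with the viral load used for the primary outcome and the questionnaire for adherence. The missing-outcome rule supports this, since it would be nearly idle under the literal reading. This reading is possible, but the text does not state it. If it is what was meant, the same short clarification is needed.

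A second reply is that completion is undefined and is a detail for the SAP. It stands in part. A reader might infer that completing the questionnaire means answering every item, so that anyone who skips a sensitive question is excluded. The article does not say so; an administered questionnaire with gaps may count. But the joint requirement itself is stated outright, not deferred.

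Third, few people may be affected. This stands. A reader might infer from the length and sensitivity of the questionnaire that many interviews will be broken off. The article gives no such rate. Trained fieldworkers administer the questionnaire in private to people who have just consented, at the same assessment as the blood draw. The order of the two is not given; if the interview comes first, someone who leaves early may have no viral load to lose.

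**Conclusion.** The point holds as a badly fixed rule of minor weight. As written, one joint set excludes observed primary outcomes for lack of a form that the primary analysis does not use, and excludes answered adherence measures for lack of a viral load. It also leaves the substitution analysis with little or nothing to do.

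The documents do not support more than that. A meaningful loss of precision is not shown: about 0.4 points of power at an assumed 5% loss, and less than 2 points at 20%. Nor is a bias of known direction or size. The effect depends on who lacks the form and whether this differs by arm, and the assumed scenarios run both ways. It would also be wrong to say that the contrast is unbiased only when completion is unrelated to suppression: with equal loss and an equal gap in both arms, the risk difference does not move at all (scenario E).

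**What to change.** Replace the shared sentence under Populations for analyses with outcome-specific sets:

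- **Primary:** all eligible consenting participants, analysed by the allocation of their clinic, using every valid post-intervention viral load whatever the questionnaire status. Missing viral loads go through the complete-case and substitution rules already planned.
- **Self-reported adherence:** all participants with the adherence items answered, whatever their viral load status.
- **Both measurements:** required only for analyses that use both, such as the per-protocol analysis of suppression by stated engagement.

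The cost is a sentence or two, with no new data collection, and the change can be made before database closure. Reporting by arm how many participants have both measures, only one, or neither would show whether the choice of set mattered.
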